#### The control intervention: standard treatment

The control group will receive standard treatment. In contrast to reablement, the standard treatment will not be time limited and thus it may continue after 10 weeks. Standard care often comprises compensating help and the content of the compensating help will be delivered according to the applications made by the participants. This may be personal or practical assistance, meals on wheels, safety alarm, or assistive technology. However, it may also involve rehabilitation by health professionals such as nurses, occupational therapists, and physiotherapists. This means that the standard treatment or care will vary among participants and municipalities.

### Training of the intervention providers and contact persons in each municipality

We will arrange a two-day course where representatives from all 44 municipalities will receive training in performing the data collection procedures, as well as designing and delivering the intervention. On the first day, an expert on COPM will give lectures and instructions, including practical exercises. On the second day, the principal investigator and project coworker will present a review of the data collection procedures. Each municipality will have a contact person who will be responsible for the different procedures employed by the project, including data collection. Each contact person will receive an evaluation pack, including all of the procedures and data collection instruments. They will also be encouraged to use videos to demonstrate how to perform the COPM interviews and the physical function tests, which comprise part of the baseline assessments. It will be important to ensure compliance with the intervention and the data collection routines. Thus, individual supervision will be provided by telephone during the intervention and data collection period, and the contact persons and health care providers will be encouraged to contact the principal investigator if they need to discuss different issues related to the project.

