## Methods/design

### Design and setting

This will be a large multicenter clinical controlled trial. The study will be conducted in primary care settings in 44 of the 428 Norwegian municipalities, including eight municipalities that function as a control group; for three municipalities with two zones, one will be assigned to the control group and the other to the intervention group (see Fig. 1 for flow diagram). The allocation of zones to the intervention or control group was based on practical reasons and decided by the municipality. The municipalities included represent 17 % of the total population in Norway. The experimental group will be offered reablement and the control group standard treatment. The sample will comprise approximately 750 participants, who will be assessed at baseline and after 10 weeks, 6 months, and 12 months.

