Compliance with the intervention and data collection procedures comprises a possible threat to the reliability of the study. This is a great challenge because a large number of municipalities are involved, as well as many different health care professionals. The reablement intervention is also individually tailored, which further increases the complexity. The intervention will vary between individuals, but also between municipalities, so it is important that all of the health care providers receive sufficient training and information. This will ensure that the correct way of implementing the intervention is understood and internalized, and that the data collection procedures are followed.

To ensure compliance with the study procedures, all municipalities will receive training. Furthermore, we will ensure that if a health professional leaves the study, then their replacement will receive sufficient training in both the intervention and the data collection procedures. In addition, the principal investigator will make regular contact with each municipality to ensure compliance with the procedures. The principal investigator will also check all of the incoming data material continuously to detect any misunderstandings and missing values, which will be corrected accordingly, if possible.

Another challenge is that the baseline COPM interview and scoring process might have a therapeutic effect, independent of the forthcoming interventions [36, 37]. The COPM interview may promote consciousness and motivation, and thus a process of change may also start in the control group, thereby diminishing the potential differences between the control and intervention groups.

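### As worded, control municipalities and both zones of split municipalities are trained to deliver reablement, an avoidable contamination risk of unknown size

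*Protocol article*

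**What the plan says.** The section on training of intervention providers and contact persons states that "representatives from all 44 municipalities will receive training in performing the data collection procedures, as well as designing and delivering the intervention". It then sets out the two days: "On the first day, an expert on COPM will give lectures and instructions, including practical exercises", and "On the second day, the principal investigator and project coworker will present a review of the data collection procedures". It also gives each municipality a contact person who is responsible for project procedures, including data collection.

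Design and setting defines the 44 as "44 of the 428 Norwegian municipalities, including eight municipalities that function as a control group", and adds that "for three municipalities with two zones, one will be assigned to the control group and the other to the intervention group".

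The Discussion restates the commitment: "To ensure compliance with the study procedures, all municipalities will receive training". It adds that anyone replacing a departing health professional will be trained in the intervention as well as in data collection. Neither statement is limited to one arm.

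The control section says of standard treatment that "it may also involve rehabilitation by health professionals such as nurses, occupational therapists, and physiotherapists".

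**The concern.** The trial compares municipalities or zones that deliver reablement with others that deliver standard treatment. Read together, the training section, Design and setting and the Discussion have representatives of the comparison sites taught to design and deliver the experimental intervention. Nothing in the article restricts that part of the training by arm, keeps staff apart in the three split municipalities, or provides a check that control care stays free of reablement components.

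If trained staff carried reablement methods into standard treatment, the two arms would become more alike. Both the COPM contrast and the cost difference would then move towards zero. The Discussion accepts dilution as a threat, but only through the COPM interview itself. Training control staff in the intervention would be a second route. Unlike the interview, which control sites need in order to measure the primary outcome, it can be avoided.

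**Working it through.** **Step 1. The text side by side.**

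| Question | Where | Answer |
|---|---|---|
| Who is trained? | Training section | Representatives of all 44 municipalities |
| In what? | Training section, opening sentence | Data collection, and design and delivery of the intervention |
| Are controls among the 44? | Design and setting | Yes: "including eight municipalities that function as a control group" |
| Do some municipalities hold both arms? | Design and setting | Yes, three, with one zone in each arm |
| Is the training limited by arm elsewhere? | Discussion | No, neither for municipalities nor for replacement staff |
| What does the listed programme contain? | Training section, day 1 and day 2 | COPM; data collection procedures |

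The opening sentence and the listed programme do not match. The first includes delivery of the intervention; the second lists no session on it. COPM does not settle the matter, because it has two roles. It is the primary outcome measure, and the Interventions section also uses the baseline COPM to steer the reablement plan. Control sites need it in the first role only.

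**Step 2. The plan's sample size, reproduced first.** Inputs from Sample size calculation: difference 1 point, SD 2.5, two-sided 5%, power 80%, and 70 control and 260 intervention evaluable (ratio 260/70 = 3.71).

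- Control n = (1.960 + 0.842)² × 2.5² × (1 + 70/260) / 1² = 7.849 × 6.25 × 1.269 = 62.3, so 63 control and 234 intervention.
- The stated 70 and 260 are somewhat larger. SE = 2.5 × √(1/70 + 1/260) = 0.337, and power = Φ(1/0.337 − 1.96) = Φ(1.01) = 84%.

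The plan's figure does not reproduce exactly but errs on the safe side. That is not part of this point.

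**Step 3. What dilution would do.** Let c be the share of the 1-point effect lost through contamination. The documents give no value, so c is an assumption shown over a range. Power = Φ((1 − c)/SE − 1.96).

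Two samples are used:
- the minimum, 70 and 260 evaluable, SE 0.337;
- about 750 enrolled (Design and setting) with 35% lost (Sample size calculation): 750 × 0.65 = 487.5, or about 103 and 384 at the same ratio, SE = 2.5 × √(1/103.4 + 1/384.1) = 0.277.

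| c (assumed) | True difference | Power, 70/260 | Power, about 103/384 |
|---|---|---|---|
| 0 | 1.0 | 84% | 95% |
| 10% | 0.9 | 76% | 90% |
| 20% | 0.8 | 66% | 82% |
| 30% | 0.7 | 55% | 72% (0.715) |
| 50% | 0.5 | 32% | 44% |

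Power of 80% needs a true difference of 2.802 × SE. That is 0.94 at 70/260 (dilution up to about 6%) and 0.78 at about 103/384 (dilution up to about 22%). None of these figures allows for clustering by municipality.

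A larger sample restores power. It does not remove the bias in the estimated effect or in the cost difference.

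**The case against.** The strongest reply is that the sentence is a loose condensation. The two listed days cover only COPM and data collection, which is about what control sites should receive, and the section heading names two audiences, intervention providers and contact persons. Course detail by arm could also sit in a full protocol. This has force and limits the point to a risk. It does not clear the text, because the article itself states who is trained in what, and the Discussion repeats it without a limit. Either control sites are trained in delivery, which is an avoidable weakness, or they are not, and the sentence misdescribes the plan.

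Several stronger readings are tempting, and the documents do not support them:

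- *Contamination is built in.* Reablement as described needs an integrated team, a joint plan, repeated training and many home visits. A two-day course for representatives does not supply these, and control sites remain assigned to standard treatment.
- *Standard treatment already contains reablement.* Rehabilitation by the same professions belongs to the declared comparator. It shows that such staff are in place, not that contamination occurs.
- *Control staff are trained before controls are recruited.* This is plausible, since the training covers baseline assessments, but the article does not date the course.
- *One contact person serves both zones.* The article gives each municipality a contact person but does not say how split municipalities are staffed.
- *Power falls to 66% or 55%.* Those figures take an assumed c and the minimum sample. The SD is also declared conservative: at 1.6, the larger value quoted from the earlier study, SE at 70/260 is 0.215 and power is about 96% at c = 20% and 90% at c = 30%.

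It is also fair to say that home-visit time by profession and service use are recorded in both groups, so unusual intensity in controls would be partly visible. Those records capture profession, frequency and minutes rather than reablement content, so they are an incomplete check.

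**Conclusion.** The concern holds as a risk created by the wording. Read with Design and setting and the Discussion, the training section has representatives of control and split municipalities trained to design and deliver reablement, although the listed course content names only COPM and data collection. If control care took on reablement methods as a result, the effect and cost contrasts would be biased towards no difference, assuming that reablement does change outcomes and costs.

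The documents neither show that this happens nor give its size. The 20% case in the working, about 66% or about 82% power depending on the sample, only illustrates the sensitivity. It rests on an assumed share, SD 2.5, a 1-point effect and no clustering. This would be one bias among several in a non-randomised comparison, but it is one that the plan can remove cheaply.

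**What to change.** Reword the opening sentence of the training section, and the matching statements in the Discussion on municipalities and replacement staff, so that:

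- only staff of intervention municipalities and intervention zones are trained in designing and delivering reablement;
- control municipalities and control zones are trained only in data collection and in COPM as a measure, with reablement training offered to them after follow-up closes;
- in each of the three split municipalities, a separate existing staff member is the contact for each zone.

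If the course has already been held, record which control-site staff received intervention training and report this as a limitation.

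Do not rely on an analysis that excludes the split municipalities. Statistical analysis and Analysis of effectiveness treat municipalities as fixed effects. Elsewhere arm is constant within a municipality, so the three split ones are the only source of a within-municipality comparison between arms at a given time.

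The cost is small: the two-day course is reorganised, and control sites wait for the reablement training.

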### Outcomes

Reablement is based on a holistic approach, so different outcomes will be used to detect potential changes in a variety of outcomes, including mental health and coping as a sense of coherence. The outcomes will also include cost outcomes such as consumption of various home-based services. These outcomes will be registered on a weekly basis during the first 6 months after inclusion. Table 2 provides an overview of the different outcomes that will be measured.

**Table 2 Tab2:** Summary of measures to be collected

Outcome	Data collection instrument and scale	Time points
Primary outcome measures		
Activity performance	Canadian Occupational Performance Measure. Scale 1–10, 1 is low performance	t1, t2, t3, t4
Satisfaction with activity performance	Canadian Occupational Performance Measure. Scale 1–10, 1 is low satisfaction	t1, t2, t3, t4
Secondary outcome measures		
Physical Performance Test	Short Physical Performance Battery, which has three parts: 1) standing balance, 2) walking four meters at regular pace, and 3) ability to stand up and sit rapidly five times. Each part is scored from 0–4 points and the total score = 0–12 points, where 0 is low performance	t1, t2, t3, t4
Health-related quality of life	European Quality of Life Scale (EQ-5D), which comprises the EQ-5D index and the EQ-5D visual analog scale (VAS). The EQ-5D index has five domains (mobility, self-care, activities, pain/discomfort, and anxiety/depression) on a five-point scale ranging from no problems to being unable. The EQ-5D VAS measures total health status on a scale 1–100 where 100 is high	t1, t2, t3, t4
Sense of coherence	Sense of Coherence Questionnaire (SOC-13). Total score ranging from 13 to 91, where higher scores indicate better sense of coherence. Responses are measured on a seven-point Likert scale (1–7)	t1, t2, t3, t4
Positive mental health	The Mental Health Continuum Short Form (MHC-SF). The MHC-SF comprises 14 items, which are scored on a six-point scale (0–5). The summary score ranges from 0 to 70, where higher scores indicate higher levels of positive mental health	t1, t2, t3, t4
Other measures		
Age	Years	t1
Gender	Female/Male	t1
Marital status	Married/Cohabiting/Single/Widowed/Separated or divorced	t1
Living situation	Living alone/Living together with someone	t1
Level of education	Primary school/High school/1–3 years University/>4 years University	t1
Current work status	Retired/Disability benefit/Working/Sick leave/Unpaid work/Unemployed/Student	t1
Motivation for rehabilitation	Numeric scale of 1–10, where 1 is low motivation	t1
Main health challenge	The most dominant health problem	t1
Other health challenges	Presence of additional health problem(s), yes/no	t1
Health status	Changes in health status in last 10 weeks, 3.5 months, and 6 months, respectively: yes/no	t2, t3, t4
Health care services and cost measures		
Warranted community-based assistance	*Frequency and type of assistance required*	t1
	Home help/Nurse/Auxiliary nurse/Occupational therapist/Physiotherapist/Mental health service/Meals on Wheels/Other assistance/No assistance	
Inpatient and outpatient treatment since last assessment	*Frequency and type of cointerventions*	t2, t3, t4
	Hospital admissions/Admissions to other institutions/Day center placement/Outpatient treatment	
Current home-based assistance offered	*Presence and frequency of home-based assistance*	t2, t3, t4
	Home help/Nurse/Auxiliary nurse/Occupational therapist/Physiotherapist/Mental health service/Meals on Wheels/No assistance	
Current community institution-based service offered	*Type of institution-based service offered*	t2, t3, t4
	Nursing home placement long-term/Nursing home placement short-term/Day placement/Other institution placement/No institution placement	
Usage of home-based services	*Weekly time registration (in minutes) of working time during home visits*	t5
	Home help/Nurse/Auxiliary nurse/Occupational therapist/Physiotherapist/Social educator/Assistant/Student/Other	

t1 = baseline assessment, t2 = 10 weeks after baseline assessment, t3 = 6 months after baseline assessment, t4 = 12 months after baseline assessment, and t5 = daily assessment during 6 months after baseline assessment

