In terms of health care service utilization, the results of a recent study showed that the participants in a reablement group required fewer home care hours, were less likely to be approved for a higher level of aged care such as nursing homes, and less likely to be in need of emergency department treatment compared with participants in a conventional care group [11]. It was also shown that people who received reablement were less likely to need personal care services [5, 12] and to be readmitted into hospital [3]. Thus, these results indicate that reablement may reduce the need for home care and other health care services.

The results are conflicting regarding the cost-effectiveness of reablement. In particular, there were no significant differences between the groups in terms of cost savings in a large clinical controlled trial [10], but the results of two other studies showed that the health and home care costs of reablement were lower than the costs of conventional home care [11, 12].

In summary, there has been insufficient research into the effects of reablement, and the results of research based on individuals and cost outcomes are inconsistent. Therefore, more research is needed to increase our knowledge of the effects of reablement.

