In the present study, the allocation of participants to the intervention group or control group will not be randomized. As a consequence, its capacity to detect causal relationships will be weaker than that in a true experimental design. However, an important strength is that this study will occur in natural settings; hence, its practicality, feasibility and, to some extent, generalizability may be high. Furthermore, the controlled design will allow us to determine whether the participants in the two groups have similar baseline levels in terms of relevant clinical characteristics such as activity performance and coping [38]. If the groups are comparable at baseline, we may be relatively confident in inferring that any posttest differences are the result of reablement. In addition, if the results indicate initial differences, these may be controlled in the statistical analyses of between-group differences.

In summary, the findings of the present study may make an important contribution to our knowledge of rehabilitation approaches for community-dwelling adults. If the reablement model proves effective, it may also be applied within other fields of rehabilitation.

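### Hospital, institutional and outpatient use is recorded only from baseline onward, so in non-randomised arms prior use cannot be compared or adjusted for directly

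*Protocol article*

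**What the plan says.** In the protocol article, Outcomes, Table 2, the block on health care services and cost measures contains the item "Inpatient and outpatient treatment since last assessment". Its categories are "Hospital admissions/Admissions to other institutions/Day center placement/Outpatient treatment", and its time points are t2, t3 and t4. The table footnote defines these: "t1 = baseline assessment, t2 = 10 weeks after baseline assessment, t3 = 6 months after baseline assessment, t4 = 12 months after baseline assessment".

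Allocation is not randomised (Sample size calculation; Discussion). In the three municipalities split into zones, the municipality chose which zone was the control, on practical grounds (Design and setting).

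The Discussion says that the controlled design allows the groups to be compared at baseline on relevant clinical characteristics. It adds that "if the results indicate initial differences, these may be controlled in the statistical analyses of between-group differences".

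The abstract lists use of health care services and costs among the things to be compared. The cost-effectiveness section takes a health care sector perspective. The Background, summarising earlier studies, reports that people given reablement were less likely to need personal care "and to be readmitted into hospital".

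**The concern.** Eligibility asks for a functional decline without saying when it began or what caused it. Someone just discharged from hospital and someone declining slowly at home can therefore both enter. These two people can be expected to differ in later admissions, in cost and in spontaneous recovery.

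In a randomised trial that mix would balance on average. Here it may differ between arms, because municipalities and zones decide who is offered what. The plan's protection is to look at baseline differences and control them, and that works only for variables measured at baseline. For prior hospital use an imbalance would not even be visible. The clinical scales all have a baseline value, whereas this service-use measure has follow-up values only.

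**Working it through.** The article gives no figure on this point, so the check is a reading of the measurement schedule followed by an illustration of size.

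**Step 1: how far back the item reaches.** The window runs from the previous assessment. The first record, at t2, therefore covers baseline to 10 weeks, and nothing before baseline is captured.

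**Step 2: whether another row covers the gap.**

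- Rows at t1: COPM performance and satisfaction, SPPB, EQ-5D index and VAS, SOC-13, MHC-SF, age, gender, marital status, living situation, education, work status, motivation, main health challenge, other health challenges (a yes/no item) and warranted community-based assistance. The last lists home help, nursing, therapists, mental health service, meals and an open category for other assistance. It has no hospital or outpatient category.
- Rows at t2 to t4 only: change in health status, current home-based assistance, current institution-based service, and the item at issue.
- The working-time registration (t5) starts after baseline.

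No row records use before baseline, and the article mentions no registry linkage.

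**Step 3: whether the planned model covers it.** The municipality fixed effects (Analysis of effectiveness) address stable municipality-level features such as size, demographics and resources. They do not address whether a given participant was recently in hospital.

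**Step 4: possible size.** With no treatment effect and no adjustment, bias = (difference between arms in the share with a recent stay) × (effect of a recent stay on the outcome). None of these inputs is in the article; all are assumptions.

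| Outcome | Assumed imbalance | Assumed effect of a recent stay | Bias |
|---|---|---|---|
| Admissions per person over 6 months, low | 0.10 | 0.1 | 0.10 × 0.1 = 0.01 |
| Admissions per person over 6 months, high | 0.25 | 0.3 | 0.25 × 0.3 = 0.075 |
| COPM change, low | 0.10 | 0.5 point | 0.10 × 0.5 = 0.05 |
| COPM change, high | 0.25 | 1 point | 0.25 × 1 = 0.25 |

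**Step 5: COPM bias against the plan's own scale.** The Sample size calculation uses a 1-point target, SD 2.5 and 70 and 260 participants.

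- The bias of 0.05 to 0.25 point is 5% to 25% of the target, or 0.05/2.5 = 0.02 to 0.25/2.5 = 0.1 SD.
- SE = 2.5 × √(1/70 + 1/260) = 0.337.
- The two-sided false-positive rate is 1 − Φ(1.96 − b/SE) + Φ(−1.96 − b/SE). For b = 0.05 this is 5.3%. For b = 0.25, b/SE = 0.743 and the rate is 0.112 + 0.003, about 12%.

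This calculation ignores clustering. A bias of the opposite sign would hide a true benefit by the same amount. No figure is offered for costs or SPPB, because the article gives nothing from which to build one.

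**The case against.** The strongest reply is that the baseline assessment is already rich. Function, quality of life, coping, mental health, main health problem, "Other health challenges Presence of additional health problem(s), yes/no t1" and required community assistance are all taken at t1. Someone recently discharged would plausibly differ on several of these, so adjustment would remove part of the confounding. This stands, and the biases above are therefore unadjusted figures. What remains is that a baseline level does not show whether a person is recovering from an acute event or declining slowly. It is also a weak stand-in for prior admissions when later admissions are the outcome.

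The Discussion does not promise control of every confounder. Its examples, activity performance and coping, are measured at t1, and it concedes weaker causal capacity. This also stands: the article does not contradict itself here.

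Hospital admission is neither a primary nor a secondary outcome, and Table 2 describes the item as a record of cointerventions. The cost-effectiveness section names home care, rehabilitation and institutional services without naming hospital admissions. A reader might infer from the Background that a readmission effect is a main claim of this trial. It is not; that sentence reports an earlier study. The item does, however, sit among the service and cost measures.

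The article is condensed and the data collection pack is not shown. That carries little weight here, because Table 2 states the time points for each row. An analysis plan can choose among collected variables but cannot add one that was never scheduled.

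**Conclusion.** The gap is real but limited. As scheduled, prior hospital, institutional and outpatient use has no baseline value, so it can be neither compared between arms nor adjusted for directly. Other baseline measures give partial, indirect control. The residual confounding that may remain bears mainly on service use and costs, and less on COPM and SPPB change.

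The size rests wholly on assumed inputs: about 0.01 to 0.075 admissions per person and 0.05 to 0.25 COPM point, before any adjustment and with unknown direction.

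Three stronger readings are not supported:

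- **That the arms do differ in recent hospital use.** Nothing in the article shows this.
- **That the bias could never be recovered.** Measured covariates capture part of it, and retrieval from records is not excluded, although none is planned.
- **That a large spurious excess in admissions should be expected.** Assuming 50% against 25% recently hospitalised, and 0.4 against 0.2 later admissions, gives 0.5 × 0.4 + 0.5 × 0.2 = 0.30 against 0.25 × 0.4 + 0.75 × 0.2 = 0.25, a 20% excess. That example takes the top of the assumed imbalance range and a doubled admission rate, so it should not be read as an estimate.

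**What to change.** Ask the existing four-category item at t1 as well, over a fixed look-back (for example the 6 months before baseline), by questionnaire or from records. Use the same source in both arms. Report it by arm in the baseline table. Enter it as a covariate (any use, and count) in the service-use and cost models and in the adjusted COPM and SPPB models.

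The cost is one extra baseline question, a slightly longer assessment and some recall error, which using records would lessen. No new instrument is needed. If baseline collection has already closed, retrieve prior use from records where that is possible. Otherwise, state in the report that recent hospital use was not measured before baseline and that residual confounding of service use and costs may remain.
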